#### 5.4.4 Discontinuation Criteria for a Subject during the Study

A discontinuation occurs when an enrolled subject ceases participation in the study, regardless of the circumstances, prior to completion of the protocol. Subjects may voluntarily withdraw from the study for any reason at any time or, if necessary, the Investigator or Sponsor may withdraw a subject from the study to protect the health of that subject. Subjects will be considered withdrawn if they state an intention to withdraw, or fail to return for visits, or become lost to follow up for any other reason.

Thus, a study subject may be discontinued from participation in the study if:

- Subject withdraws consent
- Any adverse event (AE), laboratory abnormality, inter-current illness, or other medical condition or situation occurs such that continued participation in the study would not be in the best interest of the subject
- Non-compliance with protocol requirements (e.g. use of restricted medication, urine drug screen positive, not following dosing procedures, failure to make scheduled study visits in a timely fashion)
- Wrongly enrolled subject may be discontinued from the study based on the decision taken by the designated Medical and Safety Monitor in consultation with the Sponsor (as required).
- Any other reason (as applicable) as adjudged by the Principal Investigator

The Investigator must manage the premature discontinuation /withdrawal of a study subject as follows:

- The Investigator shall determine/verify the primary reason for a subject's discontinuation/premature withdrawal from the study and record this information on the CRF.
- For subjects who are lost to follow-up (i.e., those subjects whose status is unclear because they fail to appear for study visits without stating an intention to withdraw), the Investigator should show "due diligence" by documenting in the source documents steps taken to contact the subject, e.g., dates of telephone calls, registered letters, etc.
- Discontinuation must be reported to designated Medical and Safety Monitor and Sponsor Representative without delay if it is due to an adverse event.
- If a subject terminates prematurely from the study early, all efforts will be made to complete D365 procedures for the given subject.

*All subjects who receive one dose of the vaccine will be included in the safety analysis.*

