## 7.4 Visit Schedule and Procedures

All eligible subjects will be asked to attend a total of 14 visits (Visit 1 to Visit 14).

Table 7 lists all of the assessments and indicates with an “x” against the visits at which the assessments are performed.

The subjects will be instructed to contact the investigator immediately any time after the vaccination, should they manifest with any signs or symptoms they perceive as serious.

Subjects, who discontinue the study vaccine before completing the study, and those who prematurely withdraw from the study for any reason, should be scheduled for a visit as soon as possible, at which time all of the assessments listed for the final visit (Day 365) will be performed.

If they refuse to return for these assessments or are unable to do so, every effort will be made to contact them or a knowledgeable informant by telephone to determine their health status.

*Information contained in this publication is the property of EVI and ICGEB and is confidential and will not be disclosed to third parties without written authorization from EVI and ICGEB. No part of this document may be reproduced, stored in a retrieval system or transmitted in any form or by any means -electronic, mechanical, recording or otherwise - without the prior authorization of EVI and ICGEB*

[figure not shown][figure not shown]

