### 11.3.1 Intention-To-Treat Population (ITT Population)

The ITT population will include all randomised subjects who received at least one dose of either of the assigned study vaccines. This population will be used for reactogenicity, overall safety and immunogenicity analysis.

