### 11.3.2 Per Protocol Population (PP Population)

The “Per Protocol” (PP) set includes the subjects from the ITT set who are compliant with the protocol. The PP analysis set will include all subjects who:

1. Received the randomised vaccine via intramuscular route
2. Met all eligibility (inclusion/exclusion) criteria; and
3. Developed no premature discontinuation criteria during the follow-up visits post vaccination
4. Did not take any prohibited concomitant medication during the vaccine period (up to Day 208)

This population will be used for reactogenicity and immunogenicity analysis.

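### The per-protocol reactogenicity summary excludes subjects whose reaction met a discontinuation criterion, and the protocol does not name the all-dosed set as the lead set

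*Supplement*

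**What the plan says.** **PP set (section 11.3.2).** The third condition for membership is "Developed no premature discontinuation criteria during the follow-up visits post vaccination". On use, the section says: "This population will be used for reactogenicity and immunogenicity analysis".

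**Discontinuation criteria (section 5.4.4).** One of the listed criteria is "Any adverse event (AE), laboratory abnormality, inter-current illness, or other medical condition or situation occurs", limited to one that "occurs such that continued participation in the study would not be in the best interest of the subject". The others are withdrawn consent, non-compliance, wrongful enrolment, and any other reason in the principal investigator's judgement.

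**ITT set (section 11.3.1).** "The ITT population will include all randomised subjects who received at least one dose of either of the assigned study vaccines". On use: "This population will be used for reactogenicity, overall safety and immunogenicity analysis".

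**Which set leads.** Section 11.3 applies both sets to the safety data (primary endpoints) and the immunogenicity data. Section 11.5.1.2 makes reactogenicity the primary analysis objective, summarised as binomial proportions with 95% intervals by vaccine group, and names no set. Section 11.5.1 adds the proportion who receive three doses without a grade 3 event, again with no set named. Overall safety (section 11.5.1.3) is analysed on all dosed subjects.

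**Follow-up after stopping.** Section 7.4 covers "Subjects, who discontinue the study vaccine before completing the study, and those who prematurely withdraw from the study for any reason" and calls all of them in promptly for the Day 365 assessments. The parallel text at the end of section 7.1 covers those who discontinue participation or are withdrawn, and does not mention stopping vaccine. Sections 7.2.4 and 8.5.2 require SAEs to be recorded and reported up to Day 365.

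**The concern.** A safety summary should not decide who is counted by looking at what happened to them after the dose. PP condition 3 does so. A subject whose local reaction, systemic reaction or laboratory abnormality makes continuing inadvisable fails the condition and leaves the PP numerator and denominator together. A reaction of that kind cannot appear in the PP reactogenicity table, however often the vaccine causes it.

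This is a first-in-human, dose-escalating trial with 10 vaccine recipients per dosage, so one exclusion changes the table visibly. With two reactogenicity tables planned and no lead set named, the report could put the cleaner one first without departing from the protocol.

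The follow-up wording raises a related question. SAEs to the last visit are a primary endpoint (section 4.6.1). If a subject who only stops vaccination is closed out at an early final visit, the scheduled chances of finding later events end for a group that can include those who reacted.

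**Working it through.** **Inputs.** Section 11.1.1 gives 10 vaccine and 5 control subjects in each of three cohorts: 3 × (10 + 5) = 45, which agrees with the stated total. It also says that no sample size calculation was done, so there is no powered figure to reproduce. The documents give no expected reaction rate. The reactor counts below (1 to 3 in 10) are assumptions chosen to show a range.

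**Formulas.** Let x of n dosed subjects have the reaction, and let k of those x meet the adverse-event discontinuation criterion. Then ITT = x/n and PP = (x − k)/(n − k). The difference is x/n − (x − k)/(n − k) = k(n − x) / [n(n − k)], which is never negative. Exact 95% limits are Clopper-Pearson: the lower limit is the 2.5% point of Beta(x, n − x + 1) and the upper is the 97.5% point of Beta(x + 1, n − x). With no events the upper limit is 1 − 0.025^(1/n).

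**Results for one dosage arm, n = 10.**

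| Assumed reactors | Dropped from PP | ITT (95% CI) | PP (95% CI) |
|---|---|---|---|
| 1 | 1 | 1/10 = 10.0% (0.3 to 44.5) | 0/9 = 0% (0 to 33.6) |
| 2 | 2 | 2/10 = 20.0% (2.5 to 55.6) | 0/8 = 0% (0 to 36.9) |
| 3 | 3 | 3/10 = 30.0% (6.7 to 65.2) | 0/7 = 0% (0 to 41.0) |
| 2 | 1 | 2/10 = 20.0% (2.5 to 55.6) | 1/9 = 11.1% (0.3 to 48.2) |

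Check of the first row: 1 × (10 − 1) / [10 × (10 − 1)] = 0.10, the full ITT rate.

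If no reactor meets the criterion (k = 0), this rule drops no reactor. The condition can also drop non-reactors, for example through withdrawn consent, and that moves the rate the other way (1/10 becomes 1/9 = 11.1%). The guaranteed understatement is therefore confined to reactions that meet the criterion, for which the PP count is always zero.

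**The three-dose, no-grade-3 summary.** Suppose one of 10 stops after a grade 3 reaction and the other nine complete without one. All dosed: 9/10 = 90% (55.5 to 99.7, the complement of row 1). PP: 9/9 = 100% (66.4 to 100).

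**Follow-up.** For a subject stopped at Day 14, 365 − 14 = 351 days of scheduled visits remain. Safety bloods are then due on Days 28, 56, 180, 208 and 365. Read literally, section 7.4 replaces those five draws with one early final visit. Sections 7.2.4 and 8.5.2 still require SAE reporting to Day 365, so the 351 days count scheduled contact and are a worst case.

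**The case against.** The other side has a strong case, and much of it stands.

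- **The criterion is qualified.** A reader might infer from the opening of the section 5.4.4 item that any adverse event removes a subject from PP. The rest of the sentence rules that out: the event must make continuing not in the subject's interest. A reactor who can properly continue, even at grade 3, stays in. This narrows who is dropped; those who remain affected are the reactors judged unfit to continue.
- **All-dosed reporting is already planned.** ITT is assigned to reactogenicity and overall safety, section 5.4.4 keeps everyone with one dose in the safety analysis, and section 11.5.1.3 describes adverse-event discontinuations by group. A reader might infer that the worst reactors vanish from the primary safety evaluation. They do not; they are missing only from the parallel PP table.
- **No stated decision uses the PP table.** The analysis is descriptive, and escalation rests on review of Day 14 data from all 15 subjects in a cohort. This limits the harm but does not make the table informative.
- **A separate SAP may name the lead set.** Section 11 calls itself an outline, and the SAP is not shown. That could settle the lead set. It leaves the PP definition and its assigned use, which are explicit in the protocol.
- **SAE reporting runs to Day 365 regardless.** This answers any claim that SAE capture certainly ends at the early visit. Section 8.4.7 also follows SAEs and related events after participation ends, but it concerns events already identified and does not provide for finding new ones.

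**Conclusion.** The point holds in a limited form. PP condition 3 selects on a post-vaccination outcome, and the set it defines is assigned to reactogenicity, a primary endpoint. For reactions that meet the adverse-event criterion, the PP table can only understate. In the assumed example of one such reactor in 10, the rate falls from 10% to 0% and the upper 95% limit from 44.5% to 33.6%. The size depends on the assumed counts; the zero PP count for such reactions follows from the definition. The ITT table preserves the information, so what needs correcting is a biased second table and the silence about which set leads.

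The follow-up point is secondary and is an ambiguity. Section 7.4 treats stopping the vaccine like leaving the study, section 7.1 speaks only of participation, and sections 7.2.4 and 8.5.2 expect SAE capture to Day 365. A reader might infer that 351 days of SAE data are certainly lost, or that early samples will be reported as Day 365 values. The documents establish neither. The first is a worst case, and on the second they do not say how an early-termination sample is labelled or analysed.

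**What to change.** 1. **Sections 11.3 and 11.3.2:** restrict PP to immunogenicity. Alternatively, keep a PP reactogenicity table labelled supportive, with every exclusion listed by reason and arm.
2. **Sections 11.3, 11.5.1 and 11.5.1.2:** name the all-dosed set as the set for reactogenicity and all safety, including the three-dose, no-grade-3 proportion. Carry the same statement into the SAP.
3. **Sections 7.1 and 7.4, against 7.2.4 and 8.5.2:** reconcile these so that stopping vaccination and withdrawing from follow-up are separate statuses, and a subject who stops vaccination without withdrawing consent remains under the scheduled SAE and laboratory follow-up to Day 365. State that early-termination assessments are analysed at their actual day. When vaccination should stop is a clinical matter that this change does not touch.

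Items 1 and 2 cost only wording and may save a set of tables. Item 3 uses visits already in the schedule. Their funding cannot be checked, because section 13.2 leaves financing to a separate contract that is not shown.

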## **5.6 Prohibited Prior/Concomitant Medications or Vaccines**

Following prior medications/vaccines are prohibited at study entry:

- Use of any malaria candidate vaccines at any time preceding the first study vaccination
- Use of any investigational or non-registered drug or vaccine within three (3) months preceding the first study vaccination and during the entire clinical trial period (including the follow-up period up to six months after the 3rd vaccination)
- Use of any approved vaccination or gamma globulin within three (3) months preceding the first study vaccination and during the entire clinical trial period (including the follow-up period up to six months after the 3rd vaccination)
- Chronic use (defined as use for 14 days or more) of any of the following drugs within six (6) months preceding the first study vaccination and during the entire trial period (including the follow-up period up to six months after the 3rd vaccination)
  - Immunosuppressants
  - Immune-modifying drugs
  - Oral/inhaled/systemic steroids (any dose level); *only topical steroids are permitted.*

*Information contained in this publication is the property of EVI and ICGEB and is confidential and will not be disclosed to third parties without written authorization from EVI and ICGEB. No part of this document may be reproduced, stored in a retrieval system or transmitted in any form or by any means -electronic, mechanical, recording or otherwise - without the prior authorization of EVI and ICGEB*

[figure not shown][figure not shown]

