#### ***11.5.1.4 Analysis of Immunogenicity***

Immunogenicity endpoints will be analysed at Day 28 and Day 56 compared to baseline (Day 0), and Day 56 compared to Day 28 to define the primary response to the vaccine, at Day 208 compared to Day 56 to describe the antibody levels in response to the booster dose and further at Day 180 compared to Day 56 to describe the antibody persistence of the primary vaccination, and Day 365 compared to Day 208 to describe the antibody persistence. GMTs and GMCs will be presented along with 95% Confidence Intervals.

A vaccine responder will be defined as a subject with sera reactivity by ELISA against both antigens (PfMSP-119 and PfF2) greater than background reactivity (average plus three standard deviations) of pre-vaccinated sera (17).

*Information contained in this publication is the property of EVI and ICGEB and is confidential and will not be disclosed to third parties without written authorization from EVI and ICGEB. No part of this document may be reproduced, stored in a retrieval system or transmitted in any form or by any means -electronic, mechanical, recording or otherwise - without the prior authorization of EVI and ICGEB*

[figure not shown][figure not shown]

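### The per-protocol medication check stops at Day 208 while the ban runs to about Day 360 to 366, so it is unclear who belongs in the Day 365 per-protocol antibody-persistence result

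*Supplement*

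**What the plan says.** Section 11.3.2 opens by stating that the PP "set includes the subjects from the ITT set who are compliant with the protocol" and then lists four criteria. Two of them bear on medication:

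- Criterion 3: the subject "Developed no premature discontinuation criteria during the follow-up visits post vaccination". No end day is given.
- Criterion 4: the subject "Did not take any prohibited concomitant medication during the vaccine period (up to Day 208".

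On use, the section says: "This population will be used for reactogenicity and immunogenicity analysis". It defines no separate set for each time point. The ITT set in section 11.3.1 covers immunogenicity too: "This population will be used for reactogenicity, overall safety and immunogenicity analysis".

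The ban itself is in section 5.6. For investigational products, approved vaccines and gamma globulin it applies "during the entire clinical trial period (including the follow-up period up to six months after the 3rd vaccination". For immunosuppressants, immune-modifying drugs and steroids other than topical ones it has a similar span but covers only "Chronic use (defined as use for 14 days or more) of any of the following drugs".

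Section 11.5.1.4 specifies the late comparison: "Day 365 compared to Day 208 to describe the antibody persistence".

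**The concern.** The medication criterion ends on the day the late persistence comparison begins. Take a subject who receives gamma globulin, or starts a month of oral steroids, at Day 250. He has broken section 5.6 but meets criterion 4. His Day 365 sample may reflect the product he took as well as the decay of his vaccine response. Products on the list can lower circulating antibody or add to it, so the direction of any distortion cannot be assumed.

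A PP set is normally shown beside ITT to give the view from subjects who followed the protocol. If the two sets treat medication after Day 208 alike, the PP column adds nothing on that point at Day 365. With 10 investigational subjects per dosage group, a single altered value is not averaged away.

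**Working it through.** **Inputs.** Dose 3 is on Day 180 and the last two serology samples are on Days 208 and 365 (schedule of visits, Tables 1 and 7). Each cohort has 10 investigational and 5 control subjects (section 11.1.1). The plan states no figure for this point, so there is nothing of its own to reproduce.

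**Days covered.**

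- Day 208 to Day 365: 365 − 208 = 157 days, the whole interval of the comparison.
- Share of the time from dose 3 to Day 365: 157 / (365 − 180) = 157 / 185 = 85%.
- Six months after dose 3: 180 + 6 × 30 = Day 360, or 180 + 6 × 31 = Day 366.
- Part of the ban that criterion 4 does not test: 360 − 208 = 152 to 366 − 208 = 158 days.

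**Does criterion 3 fill the gap?** Section 5.4.4 names use of restricted medication as an example of non-compliance for which a subject may be discontinued, so read literally criterion 3 could catch the Day 250 user. Three facts weaken that reading:

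1. Section 7.4.2 and Tables 1 and 7 schedule the check of discontinuation criteria at Visits 4 to 13. Visit 13 is Day 208. The Visit 14 list (section 7.4.3.14) does not contain it.
2. No visit is scheduled between Day 208 and Day 365. Medication begun in between would normally come to light in the Visit 14 medication history, where no criteria check is planned.
3. If criterion 3 already excluded every user of prohibited medication, the date in criterion 4 would have no function.

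**What each reading does to the Day 250 user.**

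| Reading | Day 365 sample | Samples to Day 208 |
|---|---|---|
| Criterion 4 governs | stays in PP | stay in PP |
| Criterion 3 or the opening sentence governs | leaves PP | leave PP, although taken before exposure |

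In a group of 10, the second reading leaves 9 at every time point because of an event after Day 208.

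**Illustration of size.** If k of n subjects have their level multiplied by f, the group GMC is multiplied by f^(k/n). The Day 365/Day 208 ratio moves by the same factor if Day 208 is unaffected. The values of f and k are assumptions; the documents give none. With n = 10:

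| Assumed change f | k = 1 | k = 2 |
|---|---|---|
| halved (0.5) | 0.93 | 0.87 |
| tenfold fall (0.1) | 0.79 | 0.63 |
| fourfold rise (4) | 4^(1/10) = 1.15 | 1.32 |

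**Scale against sampling error.** Assume a log10 SD of 0.3 to 0.5, which is not in the documents. The 95% limits for a GMC with n = 10 lie a factor of 10^(2.262 × SD / √10) either side: 1.6 for SD 0.3 and 2.3 for SD 0.5. A 15% shift sits inside that.

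**The case against.** The strongest reply is that criterion 4 is not the only gate. The opening sentence of section 11.3.2 requires compliance with the protocol. Criterion 3 asks whether a discontinuation criterion developed, not whether the subject was actually withdrawn, so the discretionary wording in sections 5.4.4 and 7.4.2 does not settle the matter. The footnotes to Tables 1 and 7 also discontinue a subject for a positive drug screen at Day 365, so discontinuation rules do not all end at Day 208. This stands to the extent that one cannot say the Day 365 PP result does include exposed subjects. A reader might infer that from criterion 4 alone, but it depends on which criterion governs and on whether such use occurs at all. Nor would any steroid or immunosuppressant use count, because section 5.6 bans only chronic use.

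Second, Day 208 is a sensible date in itself: it is 28 days after dose 3 and matches the data cut for the interim analysis (section 11.2). That supports it for samples up to Day 208, but not for the Day 365 sample.

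Third, section 11 calls itself an outline and leaves full detail to a separate SAP, which is not among the documents. The SAP may resolve this. The protocol is not silent, however: it gives a rule with a day number, and a SAP that extended the rule would depart from that text.

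Fourth, the consequence is limited. Immunogenicity is secondary, the study tests no hypothesis (sections 11.1.1 and 11.5.1), PP is not named as the main immunogenicity set, and ITT keeps these subjects by design. All of this stands and sets the weight of the point.

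**Conclusion.** Section 5.6 and PP criteria 3 and 4 do not agree on the period over which prohibited medication disqualifies a subject. The disagreement covers the full 157 days of the Day 365 versus Day 208 comparison. The PP persistence result may include subjects exposed after Day 208 or, on the other reading, may lose valid samples from earlier visits. Which of these applies cannot be settled from the protocol.

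The day counts follow directly from the schedule. The effect on the GMC, about 15% for one subject in 10 with a 4-fold shift, is illustrative only, since the documents give neither the frequency of such use nor its effect on titre. No error rate, power figure, escalation decision or primary safety endpoint is affected. The point is minor to moderate, but worth settling before the SAP is final.

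**What to change.** In section 11.3.2 and the SAP, define PP immunogenicity membership by time point. Samples taken after a subject's first prohibited medication or vaccine leave the PP immunogenicity analysis, through the Day 365 sample, and his earlier samples stay. State how criterion 3 and the opening sentence relate to this rule, so that medication use alone does not also remove the subject's earlier data. Reconcile section 5.6 with criteria 3 and 4 so that they refer to one period. For drugs banned only in chronic use, the SAP should say from which day of the course exposure counts.

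The cost is a sentence or two. Concomitant medication is already recorded at every visit including Visit 14, so no new data are needed. A few Day 365 values may leave the PP set, which makes that estimate less precise. ITT is unchanged, and the change concerns the analysis set only, not the clinical handling of any subject.
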